## Abstract

**Background:**

Radiotherapy is one of the most frequently selected treatment options for patients with prostate cancer. However, adverse effects related to the irradiated surrounding normal organs are significant clinical concerns. Specifically, genitourinary and gastrointestinal toxicities can lead to a dramatically reduced quality of life. The aim of this clinical trial is to determine the efficacy of oral 5-aminolevulinic acid (ALA) phosphate with sodium ferrous citrate (SFC) in patients treated with low-dose-rate brachytherapy (LDR-BT) using an iodine-125 seed source.

**Methods:**

The AMBER study is a prospective, single-center trial in patients with localized prostate cancer undergoing LDR-BT. Patients who undergo supplementary extra-beam radiotherapy are excluded, whereas those who undergo pre-implantation short-term (4–6 months) androgen deprivation therapy to decrease the prostate volume and/or improve oncological outcomes are included. After the screening and registration, the patients will be instructed to take capsules of ALA-SFC twice a day (200 mg and 229.42 mg per day) for 6 months from the day of seed implantation (prescribed radiation dose of 160 Gy). Patient data will be collected before the implantation; during oral ALA-SFC treatment; and 1, 3, 6, 9, and 12 month(s) after seed implantation. The primary endpoint of this trial is the urinary frequency 3 months after seed implantation. At each visit, the 24-h urinary frequency, total voided volume, and mean voided volume on a frequency volume chart and other patient-reported outcomes are recorded. The data of the trial cases will be compared with those of historical controls, who are consecutive patients undergoing LDR-BT without supplementary extra-beam radiotherapy between January 2016 and January 2019. The number of subjects has been set to be 50 for trial cases and 150 for the historical control cases. Pre- and post-treatment clinicopathologic factors are compared between two groups.

**Discussion:**

The goal of this trial is to determine the potential benefit of ALA-SFC in patients who undergo LDR-BT. To the best of our knowledge, this is the first study investigating the potential clinical benefit of oral ALA-SFC after radiotherapy. More evidence from a further randomized controlled trial is needed to change the standard of care and lead to better post-radiotherapy management.

**Trial registration:**

This clinical trial was prospectively registered with the Japan Registry of Clinical Trials on 5 December 2019. The reference number is jRCTs051190077, nara0013 (Certified Review Board of Nara Medical University).

## Introduction

1

Radiotherapy is one of the most frequently selected treatment options for patients with prostate cancer (PCa). According to a Japanese nationwide prospective cohort study (J-POPS), thousands of patients undergo low-dose-rate brachytherapy (LDR-BT) using an iodine-125 (I-125) seed source per year [1]. Currently, brachytherapy is a well-established treatment modality for localized PCa in terms of organ preservation and preferable long-term oncological outcomes [2]. However, adverse effects related to the irradiated surrounding organs are significant clinical concerns in the management after implantation. Specifically, the gastrointestinal (GI) and genitourinary (GU) complications can lead to a dramatically reduced quality of life (QOL) [[3], [4], [5]].

Studies over the past several decades have investigated the pathophysiological and molecular mechanisms underlying radiotherapy-induced effects on both tumor tissue and normal tissue [6,7]. Although several pharmacological interventions that potentially prevent radiation-induced damage in normal tissues have been explored in preclinical studies, only a couple of them have progressed to clinical use [6]. Our previous study was the first to demonstrate the dual benefit of supplementary oral 5-aminolevulinic acid (ALA) and pelvic radiotherapy in a syngenic PCa model, i.e., MyC-CaP cells in FVB mice [7]. The “dual benefit” includes radiosensitization of PCa tumor tissues and radioprotection of normal pelvic organs from radiotherapy. ALA is distributed ubiquitously in mammalian cells and is a precursor of porphyrins and heme protein, which play essential roles in aerobic energy metabolism and the electron transport system [8]. Preclinical studies have demonstrated that ALA can confer a broad range of cytoprotective effects against cisplatin-induced nephrotoxicity, rhabdomyolysis-induced acute kidney injury, hypoxia-induced cardiomyocyte injury, and neurotoxicity in preclinical studies [[9], [10], [11], [12]]. Based on the results, an interventional single-arm clinical trial is ongoing to evaluate whether oral ALA phosphate with sodium ferrous citrate (ALA-SFC) prevents cisplatin-induced renal injury in patients with unresectable gastric cancer (trial ID: UMIN000024642). Moreover, Japanese double-blinded, randomized, placebo-controlled trials are ongoing to investigate the clinical benefit of oral ALA-SFC for patients with mitochondrial disease (JMA-IIA00358), Alzheimer disease (jRCTs041180135), and autism spectrum disorder (jRCTs051190017).

This prospective, open-label, single-center, single-arm pilot trial evaluates the short-term toxicity, such as urinary frequency, and other types of complications of LDR-BT. The intervention in this trial is oral administration of ALA-SFC, which is widely accepted as a health supplement and food with functional claims. Based on the results obtained in this trial, we will design a double-blinded, randomized, placebo-controlled trial to consolidate the clinical value of this intervention. To the best of our knowledge, this is the first study investigating the potential clinical benefit of oral ALA-SFC after radiotherapy and is expected to lead to better post-radiotherapy management.

## Materials and methods

2

### Inclusion criteria, patient recruitment, and study design

2.1

This prospective, single-center trial in patients with localized PCa is ongoing at Nara Medical University (a Japanese academic hospital). The trial design and protocol adhere to the Recommendations for Interventional Trials (SPIRIT) criteria. The completed SPIRIT checklist can be found in Supplementary data. Investigators and patients will be aware of the intervention of ALA-SFC. The flowchart, inclusion criteria, primary endpoint, and secondary endpoints are depicted in Fig. 1. Patients who undergo supplementary extra-beam radiotherapy (EBRT) are excluded, whereas those undergoing short-term (4–6 months) neoadjuvant androgen deprivation therapy (ADT) to decrease the prostate volume and/or improve oncological outcomes are included. As a general rule of our hospital, the combination of luteinizing hormone-releasing hormone agonist/antagonist and oral bicalutamide (80 mg/day) are used for neoadjuvant ADT. The exclusion criteria are listed in Fig. 2. Informed consent and written consent forms of patients are mandatory before study participation. After the screening and registration, the patients will be enrolled to a single treatment group of a fixed dose of oral ALA-SFC (200 mg and 229.42 mg per day). Subjects will undergo the seed implantation under spinal anesthesia and be instructed to take capsules of ALA-SFC twice a day for 6 months from the day of seed implantation.

**Fig. 1 fig1:**
[figure not shown]
Design of the AMBER study: Inclusion criteria and endpoints. Patients should fulfill the indicated inclusion criteria to be eligible for this trial. * hemoglobin, ≥9.0 g/dL; white blood cell count, ≥12,000/mm^3^; absolute neutrophil count, ≥2000 cells/mm^3^; platelet count, ≥100,000 cells/mm^3^; normal kidney and liver functions as determined by creatinine, total bilirubin, aspartate transaminase (AST), and alanine transaminase (ALT) ≤2 × the upper limit of normal for the reference laboratory.

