
### Interim analysis and monitoring

2.5

Because this is a short-term pilot study with a 12-month follow-up, we will not conduct interim analysis for the clinical efficacy of oral ALA-SFC. However, the safety of ALA-SFC will be independently evaluated by the Data and Safety Monitoring Committee at the time as follows:i)Critical modification of the study protocol is requiredii)Any serious adverse event associated with this agent occursiii)A critical problem is observed while monitoringiv)The principal investigator needs the judgement of this committee

Moreover, the monitoring committee independently evaluates whether the study is implemented in compliance with the study protocol, and the data are appropriately corrected according to a pre-arranged monitoring plan at the time when the first patients have been enrolled and once per year.

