## Trial status

The study began in December 2019. Patient recruitment has not yet been completed and the intervention program is ongoing. A follow-up and data collection will be completed in March 2022. The final results are expected in September 2022.

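### The Fig. 1 legend requires a white cell count of at least 12,000/mm³ for entry; as printed, either the sign or the value is wrong

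*Protocol article*

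**What the plan says.** Section 2.1 does not list the inclusion criteria in the text; it points to the figure: "The flowchart, inclusion criteria, primary endpoint, and secondary endpoints are depicted in Fig. 1". The Fig. 1 legend makes them binding: "Patients should fulfill the indicated inclusion criteria to be eligible for this trial". It then sets out the laboratory limits. Haemoglobin must be at least 9.0 g/dL. The white cell line reads "white blood cell count, ≥12,000/mm^3". The next two limits are "absolute neutrophil count, ≥2000 cells/mm^3^; platelet count, ≥100,000 cells/mm^3". Creatinine, total bilirubin, AST and ALT carry an upper limit, "≤2 × the upper limit of normal for the reference laboratory".

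No other visible part of the article gives a white cell limit or a reason to select men with raised counts. The image of Fig. 1 is not available, so only its legend could be read. The Ethics section says that version 1.0 of the protocol, dated 11 November 2019, was approved; that document is not shown either.

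**The concern.** An eligibility limit is a rule that screening staff apply and readers use to judge whom the result covers. As printed, this one admits men with a high white cell count and turns away men with an ordinary one. Nothing about localized prostate cancer or brachytherapy in the article calls for that.

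The consequence depends on where else the line appears:

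- **If version 1.0 or the screening form has the same line**, either nearly every enrolled man is a protocol deviation, or enrolment was limited to men with raised counts.
- **If version 1.0 has the intended limit**, conduct is sound and only the published description of the trial population is wrong. Section 1 announces a randomised trial to follow, and its designers could copy the error.

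The point was live when the article was written: the Trial status section says "Patient recruitment has not yet been completed and the intervention program is ongoing".

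**Working it through.** **1. The line against its neighbours**

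| Item in the Fig. 1 legend | Printed limit | Type |
|---|---|---|
| Haemoglobin | ≥9.0 g/dL | permissive floor |
| White cells | ≥12,000/mm³ | floor at a raised level |
| Neutrophils | ≥2000/mm³ | permissive floor |
| Platelets | ≥100,000/mm³ | permissive floor |
| Creatinine, bilirubin, AST, ALT | ≤2 × upper limit of normal | ceiling |

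The other floors ask only for adequate counts. The white cell line makes sense as a ceiling (≤12,000) or as a floor at a lower value, but not as printed. The neutrophil floor is 2000/12,000 = 16.7% of the white cell floor, so it would add almost nothing beside it. Both ≥ and ≤ print correctly in the same sentence, so a sign corrupted when the PDF was read is unlikely.

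**2. How many men would meet the printed rule**

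The article gives no white cell distribution, so the means and SDs below are assumptions.

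- Normal model: P = 1 − Φ((12,000 − m)/s).
- Log-normal model: σ² = ln(1 + (s/m)²), μ = ln m − σ²/2, P = 1 − Φ((ln 12,000 − μ)/σ).

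Worked example for m = 7,500 and s = 2,500:

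- Normal: z = 4,500/2,500 = 1.80, so P = 0.03593.
- Log-normal: σ² = ln(1 + 1/9) = 0.1054, σ = 0.3246, μ = 8.9227 − 0.0527 = 8.8700, z = (9.3927 − 8.8700)/0.3246 = 1.61, so P = 0.05367.

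| Mean / SD (per mm³) | Log-normal P(≥12,000) | Normal P(≥12,000) |
|---|---|---|
| 5,500 / 1,500 | 0.00116 | 0.000007 |
| 5,500 / 2,500 | 0.02185 | – |
| 6,500 / 2,000 | 0.01430 | – |
| 7,000 / 2,000 | 0.01950 | – |
| 7,000 / 2,500 | 0.04192 | – |
| 7,500 / 2,000 | 0.02716 | – |
| 7,500 / 2,500 | 0.05367 | 0.03593 |

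(– = not calculated; the two normal values are the extremes of the range.)

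Share excluded:

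- Log-normal: 1 − 0.05367 = 94.6% to 1 − 0.00116 = 99.9%.
- Normal: 1 − 0.03593 = 96.4% to over 99.9%.

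A second set of assumptions points the same way. If the central 95% of counts runs from 3,300 to 8,600, 3,500 to 9,500 or 4,000 to 11,000/mm³, the log-normal share at or above 12,000 is 0.04%, 0.20% and 1.08%.

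**3. Could the printed rule have been in use?**

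The Trial status section says "The study began in December 2019" and puts the end of data collection in March 2022. Section 2.5 describes a "short-term pilot study with a 12-month follow-up". That is 27 − 12 = 15 months to enrol the 50 trial cases of section 2.4.

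At the most generous share above, 50/0.05367 ≈ 932 otherwise eligible men would be needed, or 932/15 ≈ 62 a month. At 1.08% it would be 50/0.0108 ≈ 4,600. Section 2.2 puts the centre's whole experience to November 2019 at just over 1,400 patients. The printed rule is therefore hardly compatible with the timetable.

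**The case against.** The strongest reply is that this is an obvious slip in a figure legend that nobody acted on. Men were being enrolled and treated, and the literal rule could hardly have supplied 50 of them. The serious outcome needs version 1.0 or the screening form to carry the same line, and neither is visible. The exclusion percentages come from assumed distributions and describe a rule that was probably never applied. The 16.7% ratio is weak evidence, because two floors may differ by any ratio without contradiction. A clinical reader would see the error at once, and no inference depends on it.

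Much of this stands. Conduct was probably unaffected, the percentages are conditional, and the ratio only supports the reading of the list; it proves nothing alone. But the reply accepts that the line is wrong. It is also not detail left to another document: the article states the criterion and states it wrongly. A reader who recognises the slip still cannot recover the intended limit, because ≤12,000 and a lower floor are both plausible and define different populations. Only the sponsor can settle that.

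**Conclusion.** The concern holds. The Fig. 1 legend states an eligibility limit that cannot be what was meant. Confidence is high for the misprint; it does not extend to any effect on enrolment.

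If the printed rule had been applied, it would have excluded about 95% to over 99.9% of otherwise eligible men under the assumed means and SDs. If version 1.0 carries the intended limit, the effect on conduct is zero and the published population is misdescribed. The timetable favours this second case, but that is an inference and not proof. The judgement that 12,000/mm³ is a raised count rests on general knowledge, not on a figure in the article; the conclusion is the same across every distribution tried. The sample size, primary endpoint and analysis are untouched. The line should be fixed because it is a stated entry rule and the correction is easy.

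**What to change.** 1. Compare the line with approved protocol version 1.0 and with the screening form.
2. Correct the Fig. 1 legend: reverse the sign to ≤12,000/mm³ if a ceiling was meant, or replace the value if a floor was meant. Make sure the figure itself agrees. The clinical limit is for the investigators to set.
3. Confirm from the screening log that no man was accepted or refused on the printed rule. This matters most if step 1 finds the same line in the protocol or form.
4. If version 1.0 or the form has the same line, correct it by amendment and review enrolled men against the intended limit.

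The cost is a one-line correction and a check of the log. An amendment is needed only in the case of step 4.

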**Fig. 2 fig2:**
[figure not shown]
Exclusion criteria of the AMBER study. Abbreviations: ALA, aminolevulinic acid; SFC, sodium ferrous citrate.

The use of α1-adrenoceptor antagonists to ameliorate post-seed urinary discomfort or prevent urinary retention is permitted. Prohibited medications and procedures are not set up in this trial. Medications before and after seed implantation should be recorded.

### Procedure of LDR-BT

2.2

As of November 30, 2019, we have an LDR-BT treatment experiment of more than 1400 patients. The detailed procedure of the seed implantation has been previously described [13,14]. All the patients are hospitalized for 3 nights and 4 days. The prescribed radiation dose is 160 Gy for the monotherapy. For patients without any contraindications, SpaceOAR™ hydrogel is injected between the rectum and prostate to minimize high-dose radiation to the rectum and consequent bowel side effects. Experienced radiation oncologists ([name] and [name]) calculate the post-implant dosimetric parameters based on a pelvic computed tomography scan performed about 1 month after LDR-BT.

### Follow-up, data collection, and data protection

2.3

Patient data will be collected before the implantation; during oral ALA-SFC treatment; 1, 3, 6, 9, and 12 months after the implantation; and at the end of the trial (Fig. 3). After the initiation of this trial, we provide a specific diary booklet to the participants, by which they record taking the intervention drug. At each visit, the 24-h urinary frequency, total voided volume, and mean voided volume are recorded on a frequency volume chart (FVC) over 3 days [15]. The assessment includes patient reported outcomes (PROs) such as the SF-8™, Expanded Prostate Cancer Index Composite (EPIC), International Prostate Symptom Score (IPSS), overactive bladder symptom score (OABSS), and Sexual Health Inventory for Men (SHIM) questionnaire. The data will be documented in specific Case Report Forms regarding GU/GI, hematological, and other possible toxicities using the Common Toxicity Criteria for Adverse Events (CTCAE v 5.0), complete blood count, serum chemistry, and serum prostate-specific antigen (PSA) levels. The investigators will conduct assessments for potential new or worsening adverse events as indicated in the trial schedule and more frequently if clinically needed. Biochemical recurrence is defined as the Phoenix definition of a rise in PSA level by 2 ng/mL or more above the nadir PSA [16]. When clinical recurrence is suspected, imaging examinations, such as computed tomography, magnetic resonance imaging, and/or bone scans, are performed. After discontinuation or close-out of this trial, patients will be followed up every 6 months for 5 years and annually thereafter. Discontinuation/dropout criteria are listed in Fig. 4.

**Fig. 3 fig3:**
[figure not shown]
Intervention and assessment schedule of the AMBER study according to the Recommendations for Interventional Trials (SPIRIT). Full physical examinations are required at screening and every visit. Follow-up visits and data collection should occur approximately 1, 3, 6, 9, and 12 months from the seed implantation. Patients will complete a set of questionnaires at every visit, and follow-up information may be collected via medical charts. In case of information being unavailable in chart reviews, patients may be contacted via telephone or in person. Subject identification cards may be provided after the informed consent process and prior to seed implantation. The Case Report Form will include information regarding past history, concomitant medications, and any medications taken after the treatment. Chest–abdomen–pelvis X-ray will be performed to verify seed migration. X, mandatory; (X), optional. * Hemoglobin, hematocrit, white blood cell count and fractions, platelet count; ** aspartate transaminase (AST), alanine transaminase (ALT), g-glutamyl transpeptidase (g-GTP), total bilirubin, alkaline phosphatase (ALP), lactate dehydrogenase (LDH), total protein, albumin, serum creatinine, uric acid, total cholesterol, low-density lipoprotein (LDL)-cholesterol, high-density lipoprotein (HDL)-cholesterol, triglyceride, C-reactive protein (CRP), calcium, phosphorus, potassium, chloride; *** Urine dipstick test (specific gravity, pH, protein, glucose, bilirubin, urobilinogen, ketone body, occult blood) and urine sediment test; ^†^ 3 days and nights record. Patients pick days that will be convenient for them to measure and record everything; ^††^ According to the Common Toxicity Criteria for Adverse Events (CTCAE v 5.0) translated to Japanese; ^†††^ Questionnaires: SF-8™ and Expanded Prostate Cancer Index Composite (EPIC). Abbreviations: LDR-BT, low-dose-rate brachytherapy; BW, body weight; BT, body temperature; BP, blood pressure; ECOG-PS, Eastern Cooperative Oncology Group-performance status scale; PSA, prostate-specific antigen; QOL, quality of life; IPSS, International Prostate Symptom Score; OABSS, overactive bladder symptom score; SHIM, Sexual Health Inventory for Men.

**Fig. 4 fig4:**
[figure not shown]
Discontinuation/dropout criteria of the AMBER study. Abbreviations: LDR-BT, low-dose-rate brachytherapy.

To protecting the patient data, unique identification codes will be provided to all patients. All the data will be protected in password-accessible files, and only investigators will be able to access the files. All data and documents will be deleted and discarded 5 years after the end of the trial unless the data are under secondary use for another study.

### Determining the target sample size

2.4

To date, we have been working on several clinical studies regarding oncological outcomes, adverse events, complications, and changes in urinary frequency and PROs among patients undergoing LDR-BT [3,4,14,17,18]. In this study, the data of the trial cases will be compared with historical control data. Data of patients who underwent seed implantation monotherapy between February 2016 and February 2019 will be extracted for the historical control data. The primary endpoint of this trial is urinary frequency 3 months after the implantation. One of our previous studies showed that a significant increase in urinary frequency and significant decrease in mean voided volume persisted for 12 months after seed implantation [14]. The average times per day of urination increased from 9.2 at baseline to 12.2 at 3 months after seed implantation because of bladder irritability. This observation indicated that the increase in urinary frequency was 3 times per day at 3 months, which was the peak point. To determine the required sample size of this trial, we expect that oral ALA-SFC can suppress the increase in urinary frequency to only 1 time per day and estimate the standard deviation of urinary frequency to be 3.5 times both in trial cases and historical control cases. The ratio of case numbers is set to 1:3 for trial cases and historical control cases, respectively. Given the 10% proportion of ineligible patients, the required sample size was determined to be at least 37 for trial cases and 109 for historical control cases to provide 80% power (β = 0.20) and an α level of 0.05 (two-sided). Based on the estimation, a total of 50 trial cases and 150 historical control cases will be enrolled in this study. The historical data will be obtained from consecutive patients undergoing LDR-BT with or without short-term ADT between January 2016 and January 2019. Patients who received prophylaxis with 50 mg of mirabegron (a β3-adrenoceptor agonist) just after seed implantation for decreasing undesired urgency and urinary frequency will be excluded from the historical control cases. Patients who received supplementary extra-beam radiotherapy will be excluded from the historical control cases. Pre- and post-treatment clinicopathologic factors are compared between two groups: age, body mass index, comorbidities, pretreatment urinary frequency, pretreatment PSA level, pretreatment prostate volume, biopsy Gleason score, clinical tumor stage, D'Amico risk stratification, and the post-implant dosimetric parameters.

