Assessments based on the CTCAE are the gold standard for evaluating adverse events related to treatment. However, previous studies have demonstrated that agreement between the CTCAE assessment and PROs is poor to moderate [25]. Bennett et al. reported that the rate of patients reporting severe neuropathy is 30%, which is higher than that identified by the CTCAE assessment (10%) [26]. This suggests that toxicities are often undetected or underestimated by clinicians. This trial utilizes FVCs and PROs as well as the CTCAE for toxicity assessment. Our target primary endpoint in this trial is prevention of increasing urinary frequency after seed implantation. We suppose that the benefit of this intervention will be more precisely and objectively evaluated using FVCs.

The goal of this prospective, single-center trial is to determine the potential benefit of taking ALA-FSC in patients who undergo LDR-BT. We anticipate favorable control of GU toxicities and acceptable tolerance. The potential vast utility of ALA-SFC is further encouraging because this drug can sensitize cancer cells to radiotherapy. Ultimately, the promising results will provide patients with supplementary intervention and potentially changing the standard of care.

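### The 3-month frequency endpoint is sized on a reduced increase from baseline, which fits only if trial cases and historical controls start at the same frequency; the comparison should be baseline-adjusted

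*Protocol article*

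**What the plan says.** The abstract (Methods) states: "The primary endpoint of this trial is the urinary frequency 3 months after seed implantation". Section 2.4 agrees: "The primary endpoint of this trial is urinary frequency 3 months after the implantation". Both describe a value at one time point.

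Section 2.4 then derives the effect from a rise. In an earlier study by the same group, "The average times per day of urination increased from 9.2 at baseline to 12.2 at 3 months after seed implantation", read as meaning that "the increase in urinary frequency was 3 times per day at 3 months". The expectation for the trial group and the spread come in one sentence: the investigators expect that "oral ALA-SFC can suppress the increase in urinary frequency to only 1 time per day and estimate the standard deviation of urinary frequency" at 3.5 in both groups. The spread is thus attached to the value and not to the rise. With a 1:3 ratio, 80% power, two-sided alpha 0.05 and 10% ineligible, the section arrives at 37 trial cases and 109 controls, and plans 50 and 150.

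The Discussion puts the endpoint differently: "Our target primary endpoint in this trial is prevention of increasing urinary frequency after seed implantation".

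The controls are consecutive patients treated earlier at the same centre. Section 2.4 lists pretreatment urinary frequency among the factors to be compared between the groups, but attaches no consequence to a difference. For continuous variables, section 2.6 names the Mann–Whitney U or Wilcoxon signed rank test. It mentions no covariate and does not say whether the 3-month value or the change is tested.

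**The concern.** In a randomised trial, the 3-month value and the change from baseline have the same expected group difference, so moving between them does little harm. Here allocation is by calendar period. The two expected differences then differ by exactly the gap between the groups' baseline means.

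Two things are at stake. First, the difference of 2 per day used for the sample size is a difference in 3-month values only if both groups start from the same mean. If they do not, an unadjusted test of the 3-month value mixes the treatment effect with the starting difference. Second, the value and the change can lead to different conclusions from the same data. The study is open-label and its controls were treated before it began, so the choice should be fixed beyond doubt.

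**Working it through.** **Inputs from section 2.4.** Control means 9.2 (baseline) and 12.2 (3 months); rise 3 in controls and 1 expected in trial cases; SD 3.5 in both groups; ratio 1:3; two-sided alpha 0.05; power 80%; 10% ineligible; planned 50/150.

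**Inputs assumed, because the documents do not give them.** The baseline gap between groups, the share of it still present at 3 months, and the correlation r between baseline and 3-month frequency.

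All figures use the normal approximation for a difference in means, as a guide to what a rank test would show.

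**1. Reproducing the plan's figure.** With equal baselines, the 3-month means are 12.2 and 9.2 + 1 = 10.2, a difference of 2.

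n(trial) = (1 + 1/3) × (1.96 + 0.8416)² × 3.5² / 2² = 32.05, so 33. Controls: 3 × 32.05 = 96.1, so 97 (or 99 if 33 is tripled).

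Dividing by 0.9: 33/0.9 = 36.7, so 37; 97/0.9 = 107.8, so 108; 99/0.9 = 110. The stated 37 and 109 agree within rounding. The calculation is coherent for the 3-month value, given equal baselines.

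**2. Baseline gap and the 3-month value.** Suppose the groups differ at baseline by 1 per day and half or all of this is carried forward. The 3-month comparison is shifted by b = 0.5 or 1.

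- SE at 50/150 = 3.5 × √(1/50 + 1/150) = 0.572.
- SE at 45/135 (planned numbers less 10%) = 3.5 × √(1/45 + 1/135) = 0.602.
- If trial cases start lower and the treatment does nothing: type I error = Φ(b/SE − 1.96) + Φ(−b/SE − 1.96).
- If trial cases start higher and the true effect is 2: power = Φ((2 − b)/SE − 1.96).

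| Shift b | Type I error, 50/150 | Type I error, 45/135 | Power, 50/150 | Power, 45/135 |
|---|---|---|---|---|
| 0 | 5% | 5% | 94% | 91% |
| 0.5 | 14% | 13% | 75% | 70% |
| 1 | 42% | 38% | 42% | 38% |

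Enlarging the sample does not cure the bias: the type I error is higher at 50/150 than at 45/135.

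**3. Same data, two readings.** Suppose trial cases start at 10.2 and rise by 1 to 11.2, while controls go from 9.2 to 12.2. The 3-month difference is 12.2 − 11.2 = 1, and at 45/135 z = 1/0.602 = 1.66, not significant. The difference in change is 3 − 1 = 2, and with r = 0.5 (SD of change 3.5) z = 2/0.602 = 3.32, significant.

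**4. Power if the change were tested.** If 3.5 is the SD of frequency at both times, SD of change = 3.5 × √(2(1 − r)).

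| r (assumed) | SD of change | Power at 45/135 |
|---|---|---|
| 0.3 | 4.14 | 80% |
| 0.5 | 3.50 | 91% |
| 0.7 | 2.71 | 99% |

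At the planned size, the change reading keeps about 80% power or more for r of at least 0.3.

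**5. Why adjustment resolves it.** Write the model as Y = a + gT + cB, with Y the 3-month value, T the group and B the baseline. Subtracting B from both sides gives Y − B = a + gT + (c − 1)B. The group effect g is the same for value and change. Without adjustment, a baseline gap leaves the value free of bias only if c = 0, and the change only if c = 1.

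**The case against.** The strongest reply is that nothing is miscalculated. The two places that formally define the endpoint agree on the 3-month value. The SD is labelled as belonging to that value. Describing the effect through the expected rise is simply how section 2.4 reaches 12.2 against 10.2. On this view the Discussion sentence, which names no time point, states an aim. All of this stands as far as the arithmetic goes. A reader might infer that the effect size and the 80% power belong to no defined endpoint; the reproduction of 37 and 109 rules that out.

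A reader might also infer that the trial is underpowered if change is analysed. That follows only at the stated minimum of 37/109 less 10% (about 33/98, power 67% at r = 0.3). The plan enrols 50/150, and the shortfall disappears at 45/135 unless r is below about 0.3.

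Two further points carry weight. The baseline gap is assumed, and confounding by baseline would remain under a perfectly worded 3-month endpoint. Also, the covariates may be set out in a full protocol or analysis plan not shown, Fig. 1 (which depicts the endpoints) is not visible, and the study calls itself a pilot. The article is therefore not faulted for leaving out detail. What remains is what it does state: two descriptions of the primary endpoint, an effect that needs equal baselines, and only unadjusted tests for a non-randomised comparison. Comparing pretreatment frequency between the groups would reveal a gap but would not correct for it.

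**Conclusion.** The concern holds in a limited form. The sample size is arithmetically coherent for the 3-month value but rests on an unstated assumption of equal baseline means, about 9.2 per day in both groups. Because the control is historical and the named tests are unadjusted, any baseline gap biases the primary comparison, and value and change no longer estimate the same difference.

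The size depends on assumed inputs. A shift of 0.5 to 1 per day gives type I error of about 14% to 42% at 50/150, or power of about 70% to 38% in place of 91% at 45/135, according to direction. The documents do not show that such a gap exists; they show that nothing stated in the plan would remove it. Neither an error in the sample size nor a material loss of power on the change reading is supported.

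**What to change.** 1. Name one primary variable throughout: 24-hour urinary frequency at 3 months, adjusted for baseline frequency. Align the Discussion sentence with it, and check that Fig. 1 agrees.
2. Amend section 2.6 so that the primary comparison is a baseline-adjusted model, for example ANCOVA or a rank-based equivalent. Keep the Mann–Whitney test as a supporting analysis. The identity of value and change shown above is for the linear model, so state the outcome explicitly if ranks are used.
3. Restate section 2.4 as a baseline-adjusted difference of 2 per day, with SD 3.5 as a conservative unadjusted SD. For example, at an assumed r of 0.3 the residual SD would be 3.5 × √(1 − 0.3²) = 3.34.

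The cost is a change of primary analysis method and a modelling assumption (the form of the baseline relation and a common slope in both groups). No extra patients or data are needed, since pretreatment frequency is already to be compared in both groups. The change should be made before the groups' outcomes are compared. Adjusting for baseline frequency does not remove other confounding from the historical control, and the report should say so.
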